### Statistical Analysis

Data analysis will be conducted by intent-to-treat with participants analyzed according to their randomized intervention regardless of attendance. Our primary analytical tool will be the generalized linear mixed model (GLMM) [52,53]. GLMMs accommodate multiple outcome types in a unified framework via an appropriate link function (identity link for continuous normally distributed measures; logistic link for binary measures); allow for both fixed and time-varying covariates; automatically handle missing data, producing unbiased parameter estimates provided observations are missing at random; and appropriately account for the correlations induced by repeated measurements within subjects. We will fit GLMMs with fixed effects for the intercept, time (baseline, 3, 6, and 12 months), group, and a group-by-time interaction term, where the definition of group depends on the hypothesis and an unstructured covariance matrix. Model diagnostics will be used to determine suitability of more parsimonious (eg, autoregressive) correlation structures and nonlinear (eg, quadratic) effects for time. A sample size of 330 patients will provide 90% power to detect a difference of 0.29 in the score of SDSCA between the study groups. Subgroup analysis will be performed to determine if some moderators differentially affect the outcome such as patients’ age, gender, educational levels, duration of diabetes, and baseline HbA1c levels.

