### Subject Eligibility and Recruitment Strategy

Inclusion criteria for study participants include the following: (1) aged at least 18 years, (2) being of Latinx origin speaking fluent Spanish, (3) self-report of type 2 diabetes, suboptimally controlled, defined as having HbA1c values of >7.0%, and (4) living with at least 1 adult family member who is willing to participate. Inclusion criteria of family members are as follows: (1) aged 18 years or older, (2) living in the same patient’s residence, and (3) being of Latinx origin. Exclusion criteria include (1) type 1 diabetes, (2) pregnancy, and (3) significant cognitive impairment.

Participants were recruited from the outpatient primary care clinics of Olive View-UCLA Medical Center. Recruitment began by advertising the study using flyers in the primary care clinics. Interested individuals notified staff in the primary care clinic or the study coordinator. The study coordinator discussed the study and provided further information about the project. With the individual’s permission, key relatives—significant others identified by the individual as among the most important people involved daily in his or her life—were contacted. Both the patient and the family member needed to provide informed consent for either to participate. Subject characteristics at baseline are depicted in Table 1.

**Table 1 table1:** Sample characteristics at baseline (n=330).

Variables			Overall		Nurse (n=165)		Promotore (n=165)		*P* value	
Age (years), mean (SD)			55.33 (8.39)		55.65 (8.29)		55.01 (8.50)		.48	
Education (years), mean (SD)			7.66 (4.21)		7.49 (4.03)		7.84 (4.39)		.46	
**Sex, n (%)**										.27
	Male	144 (43.64)		77 (46.67)		67 (40.61)				
	Female	186 (56.36)		88 (53.33)		98 (59.39)				
**Marital status, n (%)**										.38
	Never married	92 (27.88)		50 (30.30)		42 (25.45)				
	Married	164 (49.70)		78 (47.27)		86 (52.12)				
	Divorced	34 (10.30)		14 (8.48)		20 (12.12)				
	Widowed	15 (4.55)		7 (4.24)		8 (4.85)				
	Separated	25 (7.58)		16 (9.70)		9 (5.45)				
**Employment, n (%)**										.46
	Full-time	41 (12.42)		22 (13.33)		19 (11.52)				
	Part time	83 (25.15)		48 (29.09)		35 (21.21)				
	Homemaker	64 (19.39)		29 (17.58)		35 (21.21)				
	Retired	22 (6.67)		12 (7.27)		10 (6.06)				
	Disabled	58 (17.58)		28 (16.97)		30 (18.18)				
	Unemployed	62 (18.79)		26 (15.76)		36 (21.82)				

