### Characteristics and Training of DSME Leaders

The *promotores* were recruited from the workforce of Olive View-UCLA Medical Center (3 women and 1 man). They were of Hispanic origin and spoke fluent Spanish and English. The 3 RNs were employees at Olive View-UCLA Medical Center. All 3 spoke English and Spanish fluently. Two of the 3 RNs were of Hispanic origin. Both *promotores* and RNs were trained and certified in the Stanford Chronic Disease Self-Management program. This training included a 4-day onsite workshop in Palo Alto, California, followed by a cross-training webinar on diabetes self-management education and 2 sets of practice groups conducted at Olive View-UCLA Medical Center designed to ensure fidelity to the treatment model.

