### Initial Intervention: Tomando Control

The initial intervention, called “Taking Control of your Diabetes” or in Spanish “*Tomando Control de su diabetes*,” consisted of 6 biweekly sessions lasting 2.5 hours each led either by 2 trained *promotores* (*promotore*-led group) or by RNs (RN-led group). Each session included 10-12 patients. Patients’ families or friends were encouraged to attend sessions, which were held at Olive View-UCLA Medical Center. Each participant received a copy of the companion book, an audio relaxation tape, and an audio exercise tape with a booklet to supplement the material covered during the workshop sessions. The following topics were covered in sessions: (1) techniques to deal with the symptoms of diabetes and associated condition, (2) appropriate exercise, (3) healthy eating, (4) correct use of diabetes medications, and (5) working more effectively with health care providers in a collaborative partnership. Patients were expected to make weekly action plans, share experiences, and help each other solve problems they encountered in creating and carrying out their self-management strategies. The classes were highly participative and allowed participants to show mutual support and develop confidence in their abilities to manage their health. The program is based on the Stanford School of Medicine’s Chronic Disease Management Program developed by Lorig et al [36] and culturally adapted by Mauldon et al [37]. Similar program content was delivered in each group, with the only difference being the type of trainer: *promotore* versus RN.

Early response status was determined after the third TC session (ie, 6 weeks after starting the intervention). An independent evaluator blind to study condition used the Summary of Diabetes Self-Care Activities (SDSCA) to assess diabetes self-management behavior. A subject was considered an early responder if he/she showed a gain of 50% over baseline on the SDSCA. Early responders continued to receive the TC intervention that they were originally assigned. Nonresponders, those subjects who did not show a gain of 50% over baseline, were rerandomized to receive either the stepped-up, family-focused TC approach or the MFG. The following sections describe these 2 interventions.

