#### Ongoing MFG Sessions

Following the joining sessions and educational workshop, each cohort of 5-6 families met twice monthly for 3 months (6 sessions total). All sessions were co-led by the clinicians who conducted the 3 joining sessions. The first MFG session was focused on teaching problem-solving skills. Participants learned the mechanics of the problem-solving method and how to apply it to various problem situations. The method involves 7 steps as follows: define the problem, set goals, generate alternatives, evaluate each, select one, implement it, and evaluate outcomes. The subsequent 5 sessions were structured in the usual MFG fashion. This included a brief sharing period followed by group discussion. The discussion consisted of the sharing of personal experiences, identification of a problem situation, and the use of the problem-solving method to address the situation within the context of general group support. The group ended with review of the gains made by group members that week.

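### The stated primary model has no term for the TC class or MFG cohort, so the nurse-versus-promotore standard errors are too small if outcomes correlate within classes

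*Protocol article*

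**What the plan says.** The Statistical Analysis section lists the terms of the primary mixed model: an intercept, time (baseline, 3, 6 and 12 months), group, and group-by-time, with an unstructured covariance matrix. Group is defined by the hypothesis being tested, so it is the comparison arm and not the class a patient sat in. The correlation that the section mentions is within the patient: the models are said to "appropriately account for the correlations induced by repeated measurements within subjects". The only departures foreseen are simpler correlation structures over time and nonlinear time effects. On size, the section says: "A sample size of 330 patients will provide 90% power to detect a difference of 0.29 in the score of SDSCA between the study groups". It gives no SD, alpha, sidedness, within-patient correlation or ICC.

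Delivery is described elsewhere in Methods:
- TC: "Each session included 10-12 patients". The same section presents participation and mutual support among class members as part of how the programme works.
- MFG: "each cohort of 5-6 families met twice monthly for 3 months (6 sessions total"). These sessions are co-led.
- Leaders: 4 promotores, and "The 3 RNs were employees at Olive View-UCLA Medical Center". Leader type is the randomized first-stage factor, so leaders are nested within the H1 arms.

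**The concern.** Patients in one class share leaders, peers and discussion, and the programme intends them to influence one another. Their outcomes may therefore be more alike than those of patients in different classes. H1 compares nurse-led with promotore-led classes, so between-class variation enters the H1 contrast in full. A model that treats patients in a class as independent leaves that variation out of the standard error.

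At stake are the P value and confidence interval of the first main hypothesis. The Discussion ties that result to the cost and availability of nurses and promotores, and a falsely positive nurse advantage would favour the costlier and scarcer provider.

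**Working it through.** **Inputs from the article.** N = 330, with 165 per first-stage arm (Table 1); TC classes of 10-12, taken as 11; MFG cohorts of 5-6 families, taken as 5.5; 90% power for a difference of 0.29.

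**Inputs assumed.** Two-sided alpha 0.05; ICC 0.01, 0.02 or 0.05; 330/11 = 30 classes, 165/11 = 15 per arm.

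**1. The stated power.** The article's inputs do not suffice to reproduce it. With 165 per arm, independent patients and two-sided 0.05:
- 90% power for 0.29 at one time point requires SD = 0.29 / [(1.960 + 1.2816) × √(2/165)] = 0.81.
- If 0.29 is in SD units at one time point, power is 75.0% (83.9% one-sided).
- If 0.29 is in SD units and the mean of three follow-ups is analysed with within-patient correlation 0.5, power is 89.7%.

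So 90% is attainable under independence. The article does not say whether it was computed that way.

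**2. Class clustering, H1.** Design effect DE = 1 + (11 − 1) × ICC. Actual type I error = 2 × [1 − Φ(1.96/√DE)]. Power, starting from 90% under independence, = Φ(3.2415/√DE − 1.96), where 3.2415 = 1.960 + 1.2816.

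| ICC | DE | √DE | Type I error | 90% power becomes |
|---|---|---|---|---|
| 0 | 1.00 | 1.000 | 5.0% | 90% |
| 0.01 | 1.10 | 1.049 | 6.2% | 87% |
| 0.02 | 1.20 | 1.095 | 7.4% | 84% |
| 0.05 | 1.50 | 1.225 | 11.0% | 75% |

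With class sizes of 10 to 12, type I error is 6.1-6.3% at ICC 0.01 and 10.4-11.5% at ICC 0.05.

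**3. Simulation check.** The contrast was the mean of three follow-ups minus baseline, with 15 classes of 11 per arm, a class effect arising only after baseline, within-patient correlation 0.5, a true null, and 5,000 runs per ICC. A patient-level test rejected in 5.4%, 6.4%, 8.2% and 14.3% of runs at ICC 0, 0.01, 0.02 and 0.05. A class-level test with 28 degrees of freedom stayed between 4.5% and 5.6%. The formula is therefore not on the high side for a change contrast.

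**4. Clustering in the MFG arm only, H2.** With equal arms, DE = [1 + 1 + (5.5 − 1) × ICC]/2. At ICC 0.01, DE = 1.02 and type I error is 5.3%. At ICC 0.10, DE = 1.225 and it is 7.7%.

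**5. Interval width after correction.** Relative width = √DE × t(28)/t(328), where 28 = 2 × 15 − 2 and the t ratio is 2.05/1.97 = 1.04. This gives about 1.09, 1.14 and 1.27 at ICC 0.01, 0.02 and 0.05.

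**The case against.** The strongest reply is that the article condenses a fuller plan. The analysis paragraph does not rule out further random effects, and an SAP that is not shown could add a class term. That is possible, but the paragraph does more than name a method: it lists the model terms and the covariance structure and says which correlation is handled. As written, the dependence structure is incomplete.

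Several other objections stand and limit the point:
- A reader might infer that the type I error does exceed 5%. The article gives neither an ICC nor an alpha, and at an ICC of 0 there is no inflation.
- A reader might infer that the 90% power is overstated. That follows only if it was computed under independence, which the article does not state.
- A reader might divide each arm's patients among its 3 nurses or 4 promotores and derive a much larger leader design effect. The article does not support this: promotore classes have two leaders, nurse classes are described as led by nurses in the plural, and MFG sessions are co-led, so leaders overlap. Nor can 3 versus 4 leaders nested in arm support a well-estimated leader variance.
- A fixed class of 11 is a simplification. Nonresponders sent to MFG shared only three TC sessions with their original class, so its effect on their later outcomes may be weaker.
- Not all contact is in groups. Augmented TC adds home visits, and MFG begins with sessions held with each family separately. Each arm still includes group sessions.

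**Conclusion.** The point holds in conditional form. The stated model covers repeated measures within a patient and names nothing for TC class or MFG cohort, in a trial where every arm includes group treatment meant to work partly through the group. A positive class ICC makes the H1 standard errors too small. On the assumptions above, type I error is about 6% to 11% for ICC 0.01 to 0.05, and 90% power, if computed under independence, falls to between 87% and 75%. For H2 the inflation is milder, about 5% to 8% for ICC 0.01 to 0.10 if only the MFG arm is clustered. These are ranges over an unknown ICC, not estimates for this trial. On leaders, the article supports only a limit on inference: H1 compares these 3 nurses with these 4 promotores, and a result for the two professions in general goes beyond that.

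**What to change.** - **H1:** add a random TC-class effect on the post-baseline visits.
- **H2:** add a random MFG-cohort effect in the MFG arm only (a partially nested model), together with an effect for the original TC class.
- **Both:** use Kenward-Roger or Satterthwaite degrees of freedom (about 28 for H1 if there are 30 classes, rather than about 328) and report the estimated ICCs.
- **Power:** restate it as conditional on an assumed ICC, giving the SD, alpha and within-patient correlation used.
- **Interpretation:** state that H1 inference is limited to the participating leaders.

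The change is to analysis wording and code. It needs class and cohort identifiers from the delivery records, and no new patients or procedures. The cost is precision: H1 intervals widen by roughly 9% at ICC 0.01, 14% at 0.02 and 27% at 0.05. Because recruitment and data collection are complete, any lost power cannot be recovered by enlarging the trial.

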### Data Collection and Measures

Table 2 lists the measures to be used at each assessment point. Assessments were done at baseline and at 3, 6, and 12 months. In addition, the primary outcome variable (ie, diabetes self-management behaviors) was measured 6 weeks after the start of the first phase of the study to determine progress over time and the need for a change in treatment strategy. All measures were collected by a research assistant blind to the experimental conditions. Characteristics of the sample were measured at the initial visit including various demographic and clinical information.

The primary outcome is the difference in response scores of the SDSCA between the 4 groups at 3, 6, and 12 months after baseline [40]. The SDSCA is a well-validated instrument with excellent psychometric properties in several languages including Spanish [41,42]. It is the instrument most frequently used for assessing the acquisition of diabetes self-management behaviors [43]. The SDSCA is formatted to ask on how many of the previous 7 days the individual performed recommended self-management activities: eating healthy foods, following a diabetic diet, exercising, self-monitoring of glucose, and caring for one’s feet. A weekly self-care score ranging from 0 to 7 is generated, with higher scores corresponding to greater number of days carrying out the recommended behaviors.

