Demographics	UCLA Client Data Inventory Cuellar acculturation scale Structured Clinical Interview for DSM-IV (SCID-I)	Age, gender, marital status, work status, educational level, acculturation level, and medical/psychiatric disorders	T1
Diabetes self-management	Revised Summary of Diabetes Self-Care Activities (SDSCA)	Assesses adherence to diet, exercise, self-monitoring, medications, and foot care	T1-T4 and week 6
Diabetes self-efficacy	Stanford Self-Efficacy Scale	Measures confidence to self-manage diabetes	T1-T4
Diabetes knowledge	Spoken Knowledge in Low Literacy Diabetes Patients (SKILLD)	Assesses knowledge of T2DM and its management	T1-T4
Family support	Diabetes Family Support Behavior Checklist	Assesses family support for T2DM self-management	T1-T4
Collaborative goal setting	Patient Assessment of Chronic Illness Care (PACIC)	Evaluates quality and patient centeredness of received treatment	T1-T4
Treatment attendance	Treatment Attendance Log	The percentage of sessions attended by patient/relative	T3
T2DM control	Bayer A1C NOW kit	Hemoglobin A1c level	T1-T4

^a^Data collection schedule: T1: baseline; T2: 3 months; T3: 6 months; T4: 12 months.

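### The SDSCA model treats baseline as a free outcome and leaves out the week-6 score taken before rerandomization, which costs precision (not validity), most of all in the nonresponder comparison

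*Protocol article*

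**What the plan says.** Statistical Analysis writes the model out: "We will fit GLMMs with fixed effects for the intercept, time (baseline, 3, 6, and 12 months), group, and a group-by-time interaction term". One form serves every hypothesis, "where the definition of group depends on the hypothesis and an unstructured covariance matrix". The section notes that mixed models can take covariates, but it names no adjustment for baseline or week 6.

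The week-6 score exists. Data Collection and Measures says the primary outcome variable "was measured 6 weeks after the start of the first phase of the study to determine progress over time", and Table 2 schedules the SDSCA at "T1-T4 and week 6". Initial Intervention: Tomando Control places the measurement before the second randomization: "Early response status was determined after the third TC session (ie, 6 weeks after starting the intervention". It then says "Nonresponders, those subjects who did not show a gain of 50% over baseline, were rerandomized".

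**The concern.** At the first randomization the two arms have the same expected baseline mean. A model with a free group effect at baseline plus group-by-time ignores this. If the test is the interaction, each arm's follow-up is compared with its own noisy baseline. If the test is the difference at follow-up, the baseline contributes nothing. Both waste information.

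In the nonresponder comparison the study baseline is a remote reference, because it precedes three sessions common to both options. The measurement closest to the second randomization is week 6, and the model has no place for it. This comparison also uses only part of the 330 patients, so lost precision matters more here. At stake are wider confidence intervals and lower power than the collected data could give.

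**Working it through.** **Inputs from the article.** First-stage arms of 165 and 165 (Table 1). Time levels of baseline, 3, 6 and 12 months. SDSCA also at week 6. The stated power: "A sample size of 330 patients will provide 90% power to detect a difference of 0.29 in the score of SDSCA".

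**Inputs not in the article, assumed here.** SD, two-sided 5% level, correlation r between visits, dropout and nonresponder share.

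**The plan's own figure.** With 165 per arm and SD 1 at a single visit, the standard error is √(2/165) = 0.110. Then 0.29/0.110 = 2.63, and power is about 75% two-sided. An SD of 0.81 gives 90%. So does an average of three follow-up visits with SD 1 and r = 0.5 (89.7%). The 90% can be neither confirmed nor refuted. SD 0.81 is used below for illustration only.

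**H1, variance per patient at one visit, in units of SD².**
- Change from a free baseline: 2(1 − r)
- Difference at follow-up, baseline free: 1
- Baseline constrained equal or adjusted: 1 − r²

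Excess variance of the plan is 2/(1 + r) − 1 for the change contrast and 1/(1 − r²) − 1 for the follow-up contrast.

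| r | Change contrast | Follow-up contrast | Detectable difference at 90% power, change → adjusted (SD 0.81) |
|---|---|---|---|
| 0.4 | 43% | 19% | 0.318 → 0.266 |
| 0.5 | 33% | 33% | 0.290 → 0.251 |
| 0.6 | 25% | 56% | 0.259 → 0.232 |

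**H1, adding week 6 as an outcome visit.** With complete data and free means at each visit the gain is exactly zero. With 20% to 25% dropout, the generalized least squares variance falls by about 1% to 3%.

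**H2, analytic illustration.** Under equal correlation r, adjusting for baseline and week 6 leaves 1 − 2r²/(1 + r). At r = 0.5 this is 1 − 0.5/1.5 = 0.667, against 1.00 for change from a free baseline and 0.75 with baseline alone. If 70% are nonresponders, there are 330 × 0.70/2 ≈ 116 per option. Power for 0.29 with SD 0.81 is then 77% (plan), 88% (baseline adjusted) and 91% (both). For nonresponder shares of 50% to 90%, it goes from 63%–87% under the plan to 80%–97% with both.

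**H2, allowing for selection.** Nonresponders are selected on week 6 relative to baseline, so correlations among them differ from those in all patients. A simulation kept patients with week 6 below 1.5 × baseline and clipped scores to 0–7. It used baseline means of 2.5 to 4.5, gains of 0.3 or 0.8, SD 0.81 or 1.3, and correlations that were exchangeable at 0.5 or 0.6 or decaying with time. Nonresponder share ranged from about 60% to 98%. Residual variance relative to change from a free baseline:
- baseline adjusted: 0.75 to 0.92
- baseline and week 6 adjusted: 0.60 to 0.83
- removed by week 6 beyond baseline: 7% to 20%

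Since 1/0.83 = 1.20 and 1/0.60 = 1.67, the gain equals about 20% to 67% more nonresponders. With exchangeable correlation 0.5, the simulated ratio is 0.70 to 0.81. If the planned change variance is held as in the 70% illustration (0.29/SE = 2.71), 2.71/√0.81 = 3.01 and 2.71/√0.70 = 3.24. Power is then about 85% to 90%, slightly below the unselected 91%.

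**The case against.** The planned model is standard and valid. The first hypothesis speaks of greater increases, which the group-by-time term tests directly, and an article may leave covariate lists to a fuller plan. Validity is granted: this is a choice between valid analyses. The appeal to a fuller plan has less force, because the article lists the model terms and time points and week 6 is not among them.

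The article does not fix the contrast, and the two formulas move in opposite directions as r rises. That stands, so both are shown. Precision is lost under either.

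A reader might infer three stronger things, none of which the documents support:
- **That week 6 would sharpen H1.** It adds nothing with complete data and very little with dropout. The H1 loss comes from the baseline alone.
- **That the H2 loss equals about 70% more patients.** Assumed correlations with the outcome of 0.5 (baseline) and 0.6 (week 6), and 0.5 between them, give R² = (0.25 + 0.36 − 0.30)/0.75 = 0.413, and 1/0.587 = 1.70. Those correlations ignore the selection of nonresponders, and the result lies above the simulated range.
- **That leaving out week 6 undermines the missing-at-random assumption or biases the results.** No dropout rate or mechanism is given, and within H2 every patient is a nonresponder, so response status does not vary. Chance imbalance at week 6 is already reflected in the standard error.

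A change of model after data collection also needs justification. That stands and shapes the fix.

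**Conclusion.** The concern holds as a loss of precision. With complete data the published model's contrasts remain unbiased under randomization. For H1 the excess variance is 25% to 43% for the change contrast, or 19% to 56% for the follow-up contrast, over assumed correlations of 0.4 to 0.6; all of it comes from the free baseline. For H2 the adjusted analysis keeps about 0.60 to 0.83 of the planned variance, with week 6 contributing 7% to 20% beyond baseline. The direction is secure. The sizes rest on assumed correlations, SDs and nonresponder shares. The change is worth making, chiefly for H2, where the sample is smaller and the omitted score is the natural covariate.

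**What to change.** - **H1:** constrain the baseline SDSCA means to be equal across arms, or use baseline SDSCA as a covariate for the follow-up visits. Week 6 falls after the first randomization, so it may enter only as an outcome visit, never as a covariate.
- **H2:** among rerandomized nonresponders, analyse 3, 6 and 12 months with baseline SDSCA, week-6 SDSCA and first-stage arm as covariates. All three precede the second randomization. State how a missing week-6 score is handled.
- **Both:** name the contrast and the visit or visits it covers.

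No new data are needed, but the cost is more than analysis code. The article's Results section says data collection ended in December 2021 with analysis still to come, and its limitations say investigators knew the assignments. The change should therefore be documented and dated before outcomes are examined, with the published model reported as a sensitivity analysis. If outcomes have already been examined, the report should say so.

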### Group Versus Individual Sessions

The type and setting of these interventions may also be important, and one question that has received some attention is that of group versus individual sessions. One study that tested the “dosing” of an individual DSME found that 16 hours of education with an additional 6 hours of group support was as effective as 52 individual contact hours delivered over 12 months [6]. There are also 4 studies that have directly compared individual with group DSME; three of these led to the conclusion that group education appeared to have a greater impact on diabetes self-management and glycemic control than individual education at 6 and 9 months [27]. However, these were described as poor studies with small numbers and high dropout rates, and there was no significant difference between the interventions at 12 and 18 months. The fourth study did find that patients with T2DM of relatively long duration and HbA1c levels of 7% or higher had improved short-term HbA1c outcomes and a greater likelihood of achieving an HbA1c level below 7% if they were educated using the group approach versus the individual method; however, in this study, the total educator contact time was also greater for the group intervention (8 hours) than for the individual approach (3 hours) [28].

Some families may require extra efforts, such as home visits, telephone reminders, and cultural tailoring, to address the specific obstacles to attendance faced by families [9]. However, other families may need a far more intensive approach to encourage and sustain their participation in DSME, including multifamily groups (MFGs). Two lines of research support the value of MFGs for this purpose. First, randomized controlled studies of MFG in adolescents with type 1 diabetes have shown improvements in diabetes self-care, particularly in patients with poorer glycemic control at baseline [29,30]. Second, the MFG approach has been shown to improve self-management skills in a Mexican American population with chronic mental illness [31]. Given that this study was carried out with a hard-to-reach community of Spanish-speaking Mexican American individuals and that psychiatric symptoms (eg, depression, anxiety, and psychosis) have been identified as major impediments to use diabetes self-management practices [32-35], the results suggest that the MFG approach may be effective in this population.

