### Hypothesis

There are 4 main hypotheses this study will test. First, subjects randomized to adaptive interventions that begin with nurse-led groups will show greater increases in diabetes self-management behaviors than those who begin with *promotore*-led groups. Second, among nonresponders to either of the first-line approaches, subjects randomized to a multifamily, problem-solving group will show greater improvements than those assigned to a single-family approach. Third, key relative’s participation in treatments will lead to (1) increased patients’ and relatives’ diabetes knowledge; (2) increased diabetes self-efficacy; (3) increased collaborative goal setting by families with health care providers; (4) increased family support; and (5) increased T2DM self-management behaviors. Fourth, subjects who are older, female, less educated, and less acculturated have an alcohol use or psychiatric disorder or have a longer history and greater severity of T2DM will (1) be less likely to have family members participate in treatment and (2) use diabetes self-management skills less often.

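### The models for Hypotheses 1 and 2 are valid but omit baseline variables that the plan itself expects to predict the SDSCA; a short prespecified covariate list would bring a modest gain

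*Protocol article*

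**What the plan says.** The Statistical Analysis section of the protocol article sets out the model: "We will fit GLMMs with fixed effects for the intercept, time (baseline, 3, 6, and 12 months), group, and a group-by-time interaction term". Group is redefined for each hypothesis, and the covariance is unstructured. Baseline SDSCA is therefore one of the four repeated responses. The section says that mixed models in general "allow for both fixed and time-varying covariates", but names no covariate for Hypothesis 1 (nurse-led versus promotore-led start) or Hypothesis 2 (multifamily versus single-family approach in nonresponders). On missing data it says that these models "automatically handle missing data, producing unbiased parameter estimates provided observations are missing at random".

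Hypothesis 4 concerns patients described as follows: "subjects who are older, female, less educated, and less acculturated have an alcohol use or psychiatric disorder or have a longer history and greater severity". It predicts less frequent use of self-management skills in them. The section Group Versus Individual Sessions adds that "psychiatric symptoms (eg, depression, anxiety, and psychosis) have been identified as major impediments" to self-management. Table 2, under Data Collection and Measures, schedules at baseline "Age, gender, marital status, work status, educational level, acculturation level, and medical/psychiatric disorders", and HbA1c as well. It does not list alcohol use disorder or diabetes duration by name. Duration and baseline HbA1c appear among the moderators in Statistical Analysis. The article uses these variables only for subgroup analyses and, in Principal Findings, as exploratory predictors of outcome.

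**The concern.** By the plan's own reasoning, several variables that it measures or intends to use are prognostic for the primary outcome, and the stated treatment models use none of them. Two things could be lost.

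- **Precision.** Outcome variation that these variables explain stays in the error term.
- **Robustness to missing data.** Missing at random holds or fails given what is in the model. If dropout depends on, say, psychiatric disorder, and does so differently in the two arms, a model without that variable does not cover it. Hypothesis 2 is where this is most conceivable, because the arms differ in burden: three joining sessions, a 6-hour workshop and six group sessions for multifamily treatment, against up to three home visits and three sessions for the augmented program.

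**Working it through.** **Inputs.** From the article: 330 patients, 165 per arm, 90% power, difference 0.29. Not given, so assumed: two-sided 5% level; covariates explaining R² = 2%, 5% or 10% of residual variance; correlation between visits 0.5; 60% nonresponders (198 patients, 99 per arm) for Hypothesis 2; all dropout rates.

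**1. The stated power.** No SD is given, so the 90% can be neither reproduced nor refuted. It implies SD = 0.29 / [(1.960 + 1.282) × √(2/165)] = 0.813, which is used below as the residual SD.

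**2. Score difference at one visit.** The standard error is multiplied by √(1 − R²), and the equivalent sample size is 330/(1 − R²). For Hypothesis 2 without covariates, the standard error is 0.813 × √(2/99) = 0.1155, the ratio is 0.29/0.1155 = 2.51, and power is Φ(2.51 − 1.96) = 70.9%.

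| R² | Standard error falls by | Equivalent N | Power, Hypothesis 1 | Power, Hypothesis 2 |
|---|---|---|---|---|
| 0 | – | 330 | 90.0% | 70.9% |
| 2% | 1.0% | 337 | 90.6% | 71.8% |
| 5% | 2.5% | 347 | 91.4% | 73.1% |
| 10% | 5.1% | 367 | 92.7% | 75.4% |

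**3. Difference in change from baseline.** With complete data the standard error in SD units is √(4/330) × √[2(1 − ρ)], which is 0.1101 at ρ = 0.5. A covariate whose effect is the same at every visit cancels from the change, so the standard error stays at 0.1101 whatever its R². If the effect grows from zero at baseline to its full size at 12 months, and a covariate-by-time term is fitted, the standard error becomes 0.1101 × √(1 − R²): 0.1073 at 5% and 0.1044 at 10%.

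**4. Missing-data illustration for Hypothesis 2, with no true effect.** A factor present in 30% of patients lowers the SDSCA by d. Dropout is higher for patients with the factor in the multifamily arm only, and is the same for everyone else.

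- Mild case: d = 0.5, dropout 40% versus 15%. Factor prevalence among multifamily completers is 0.18/(0.18 + 0.595) = 0.232. The completers' difference is 0.5 × (0.300 − 0.232) = 0.034.
- Strong case: d = 0.8, dropout 50% versus 10%. Prevalence is 0.15/(0.15 + 0.63) = 0.192. The completers' difference is 0.8 × (0.300 − 0.192) = 0.086.

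Those values would be the bias if the factor left baseline SDSCA untouched. Hypothesis 4 implies that it lowers baseline too, and baseline is in the model. The bias is then the completers' difference times (1 − β), where β is the slope of follow-up on baseline. With residual variance 0.813² = 0.661, residual covariance half of that, and factor variance d² × 0.3 × 0.7:

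- Mild: β = (0.3305 + 0.0525)/(0.661 + 0.0525) = 0.537; bias 0.034 × 0.463 = 0.016, about 5% of 0.29.
- Strong: β = (0.3305 + 0.1344)/(0.661 + 0.1344) = 0.584; bias 0.086 × 0.416 = 0.036, about 12% of 0.29.

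Dropout after later visits gives less bias, because the model also uses the visits already observed. If the factor acts on dropout in the same way in both arms, prevalence among completers is equal and the bias is about zero. Putting the factor in the model removes the bias in both cases.

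**The case against.** The case for leaving the plan alone is strong in several respects.

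- An unadjusted randomized comparison is valid. The sentence is a general model outline in a condensed article: it cannot be exhaustive, since neither Hypothesis 4 nor the moderator analyses can be fitted with those terms alone. A covariate list may stand in the full protocol or analysis plan. This stands, and it rules out calling the model an error.
- Hypothesis 4 is a hypothesis, and it concerns the level of self-management, not change. Hypothesis 1 is worded as greater increases, where step 3 shows no gain from a constant effect. This also stands. It is limited by Data Collection and Measures, which words the primary outcome as a difference in scores at 3, 6 and 12 months, where step 2 applies.
- No dropout figure is given, and nothing ties dropout to these variables differently by arm. Missing sessions is not the same as missing outcomes, because patients are analyzed as randomized whatever their attendance. This stands, so step 4 is an illustration only.

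A reader might go further on two points that the document does not support. One is that the sex imbalance in Table 1 (53.3% women in the nurse arm, 59.4% in the promotore arm) tilts Hypothesis 1 toward nurses. With P=.27 this is ordinary chance variation, which the standard error already covers. A constant sex effect cancels from a change contrast, and age and education lean the other way. The other is that the plan wrongly calls its estimates unbiased. Its statement is conditional: "producing unbiased parameter estimates provided observations are missing at random".

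**Conclusion.** The point holds as a minor recommendation. The stated models for Hypotheses 1 and 2 are valid, but they make no use of baseline variables that the plan itself treats as prognostic. The gain for a score difference at a visit is about 0.6 to 2.7 percentage points of power for Hypothesis 1, and about 1 to 4.5 points for Hypothesis 2, if R² is 2% to 10%. For a change contrast with complete data it is nil unless the covariates predict change. The missing-data benefit is about 0.016 to 0.036 SDSCA points in the assumed scenarios where the factor also lowers baseline, and about zero if dropout follows the same pattern in both arms. The R², SD, correlation, nonresponder share and dropout rates behind these figures are assumptions, because the article gives none of them.

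**What to change.** In Statistical Analysis, name a short list of baseline covariates for the Hypothesis 1 and 2 models before the data are analyzed, and do not select them by P value. An example is age, sex, years of education, psychiatric or alcohol use disorder, diabetes duration and baseline HbA1c. Enter them with time where the contrast is a change. Report the model without them as a sensitivity analysis, and state that missing at random is assumed conditional on the listed covariates.

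The cost is a few lines of text and, as far as Table 2 and the moderator list show, little or no new data. Six covariates at four visits add 24 parameters (6 × 4). That is slight against 330 patients but more noticeable in the smaller Hypothesis 2 sample (198 under the assumption above), so the list should stay short. A simple rule for missing covariate values is also needed.
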